## Abstract

**Background:**

Perinatal anxiety is common: up to 40% of pregnant women and new mothers experience high levels of anxiety. Given its prevalence, interventions that are low-intensity, highly accessible and cost-efficient, and target modifiable risk factors for anxiety are needed. Repetitive negative thinking (RNT)—such as worrying about ways things will go wrong in the future or ruminating about past negative events—is a risk factor for the development of anxiety. RNT is maintained by the tendency to generate negative interpretations of ambiguous situations.

**Methods:**

A parallel two-arm randomised controlled trial will assess the efficacy of adding interpretation training (RELAX) to usual maternity care. Participants (*N* = 268) will be randomised to (i) 12 sessions of online interpretation training (RELAX) plus usual care, or (ii) usual care alone. We will assess anxiety, depression, RNT, and work and social adjustment at baseline, plus 4, 8 and 36 weeks later.

**Discussion:**

Should the intervention result in lower levels of anxiety than usual care, it could be an accessible, cost-effective way to help women who are vulnerable to experiencing anxiety in the perinatal period.

**Trial registration:**

ISRCTN 12754931. Registered 25th May 2023, prior to recruitment.

## Administrative information

Note: the numbers in curly brackets in this protocol refer to SPIRIT checklist item numbers. The order of the items has been modified to group similar items (see http://www.equator-network.org/reporting-guidelines/spirit-2013-statement-defining-standard-protocol-items-for-clinical-trials/).

## Introduction

### Background and rationale {6a}

Anxiety is common in the perinatal period, with up to 40% of pregnant women, and new mothers reporting high levels of anxiety [1]. Perinatal anxiety is associated with multiple significant adverse consequences, including reduced maternal responsivity to infants [2], impairments in childhood development, and a twofold increase in risk of a child developing psychological disorders [3]. Despite its documented prevalence and consequences, perinatal anxiety has received minimal research attention to date (in particular, relative to postnatal depression; [4, 5]). A limited number of treatment trials have evaluated psychological interventions for perinatal anxiety (see [6–9] for reviews) and have typically included women with high levels of anxiety or diagnosed anxiety disorders in the antenatal [10–13] and postnatal [11, 14] periods. Whilst it is no doubt clinically important to treat perinatal anxiety once it has emerged, it is equally important to explore the potential of early interventions targeting established risk factors to prevent or mitigate the development of anxiety symptoms later in the perinatal period.

Of the studies that have explored prevention in at-risk groups, most have tested multicomponent cognitive behavioural therapy (CBT) packages [15]. A limitation of this approach is that it precludes determining the specific treatment component/s that are most effective and deliver the most clinical benefit. In addition, these studies target cognitive and behavioural processes that play a role in psychopathology generally, rather than processes that have been established as predicting and maintaining psychological distress in the perinatal period specifically. Accordingly, an alternative approach is to target one identified, modifiable risk factor that predicts and maintains perinatal anxiety. Furthermore, interventions that target individuals who are identified as being at-risk of psychological problems are more effective than non-targeted universal approaches. Targeted preventative online interventions in particular are simpler to disseminate and deliver at scale. Moreover, online interventions such as LENS do not necessitate delivery by clinicians with specialist CBT training. Given this, there is a clear need for efficacious, evidence-based early-interventions which target known modifiable psychological risk factors which confer vulnerability to perinatal anxiety.

The tendency to engage in repetitive negative thinking (RNT)—worrying about the future and ruminating about the past—is an established risk factor for anxiety. Levels of RNT about a stressful life-event predict subsequent anxiety symptoms [16]. Pregnancy, birth, and adjustment to motherhood are potentially stressful and often characterised by uncertainty, and thus have the potential both to trigger and serve as a focus of RNT. Consistent with this, we have demonstrated a link between perinatal RNT and anxiety in pregnant [17] and postnatal [18] women. Our recent review [19] highlighted consistent evidence of associations between RNT and both depression and anxiety in pregnancy and postpartum. Moreover, worry in pregnancy was a consistent predictor of later (i.e. antenatal and postnatal) anxiety and depression [19].

No study to date has tested the possibility that an early intervention offered to those with RNT in pregnancy could result in lower anxiety later in the perinatal period. This is surprising given that we have effective interventions for RNT in the general population preventing the onset of later psychopathology. For example, Topper et al. [20] found that an intervention targeting RNT in young adults who reported high levels of RNT (i.e. Rumination-focused CBT [21]) resulted in less anxiety 12 months later. As a modifiable risk factor that predicts perinatal psychological distress, we propose that similarly targeting RNT early in pregnancy may result in less escalation of anxiety over the perinatal period. Such an intervention would need to be tailored to the unique experiences and challenges of pregnant women.

There is evidence that RNT is linked to a negative interpretation bias; that is, the tendency to interpret unclear or ambiguous information in a negative (rather than positive or benign) manner. A negative interpretation bias is a transdiagnostic process characteristic of individuals with a range of emotional disorders [22]. Hirsch and Mathews’ [23] cognitive model of RNT proposes that interpretation bias maintains RNT. In accord with this, there is evidence that RNT is associated with interpretation bias in non-pregnant clinical and non-clinical populations [24], and also in pregnant women [17]. Given the ambiguous nature of stressful situations during pregnancy (e.g. “will the scan show that my baby is ok?”), there are frequent opportunities to make negative interpretations (e.g. “the scan will find something wrong”) that fuel RNT, in turn escalating anxiety.

Cognitive bias modification (CBM) was initially developed as an experimental paradigm to investigate the downstream impact of manipulating cognitive biases (e.g. in interpretation, attention) on psychological symptoms. CBM has subsequently been employed to train individuals from populations characterised by unhelpful biases to adopt more adaptive alternatives (e.g. CBM to train positive interpretations of ambiguous stimuli, known as CBM-I), thus exploring its clinical utility. Hirsch et al. [25] found that 10 sessions of CBM-I which trained positive interpretations, compared to an active control condition, reduced both worry and anxiety at 1 month follow-up in people with a diagnosis of generalised anxiety disorder (GAD), compared to an active control condition. Similar findings emerged in a study with a community sample with high RNT (worry and/or rumination): participants who received CBM-I reported lower anxiety, depression and RNT at 1-month follow-up, relative to an active control condition [26], particularly when interpretation training incorporated imagery of the positive outcomes. In a GAD sample, Hirsch et al. [27] evaluated the effectiveness of the imagery enhanced multi-session CBM-I training delivered fully online (i.e. with no face-to-face researcher contact) relative to a control condition, and replicated these effects at 3-month follow-up. In addition, they reported high compliance with the intervention and excellent retention rates for follow-up assessments. Hirsch et al. [27] also demonstrated that the purported mechanism of change—interpretation bias—was effectively targeted by the intervention, and that the impact of CBM-I on reducing interpretation bias mediated effects on anxiety and worry.

Whilst these initial findings were promising, given the unique circumstances of the perinatal period (e.g. profound physical, hormonal, emotional and social changes), we could not assume that the mechanisms underpinning RNT (nor the interventions that address them) are the same in pregnant and non-perinatal samples. Accordingly, we conducted a proof-of-principle study [28] to examine whether a single session of CBM-I could effectively modify interpretation bias in pregnant women (≥ 16 weeks gestation) with high levels of worry. Relative to participants in the active control condition (in which the ambiguous scenarios were also presented but remained unresolved), those who received CBM-I generated more positive interpretations and reported fewer thought intrusions (on a behavioural worry measure). Thus, CBM-I effectively induced a positive interpretation bias and resulted in less negative thought intrusions (a proxy for worry) in pregnant women who were high worriers, raising the possibility of its capacity as an intervention to target RNT in the perinatal period.

To increase the accessibility and uptake of psychological treatment in the perinatal period, research has focused on the development and evaluation of online interventions [29, 30]. Online interventions have the potential to increase access to psychological interventions for expectant and new mothers, for whom there are likely to be multiple practical barriers to attending therapy in a clinical setting. Moreover, they also reduce the burden on typically over-stretched perinatal mental health services, leaving capacity available for those who need specialist input. Indeed, our extensive Patient and Public Involvement and Engagement (PPIE) work indicates that interventions during pregnancy, rather than post-birth are favoured, given that women would have more time to complete our brief (20-min sessions) when pregnant, rather than when they are adapting to the challenges and responsibilities associated with caring for a newborn and are sleep deprived. They also felt that an online intervention that they could complete when and where works for them would be particularly helpful since it would negate the costs of travel and provide flexibility around work, childcare and other responsibilities. They also mentioned that they would like to hear about the intervention via both NHS services and non-NHS routes, such as third sector organisations that support women over the perinatal period or social media. The development of a low intensity (self-help), highly accessible, cost-effective intervention to address perinatal anxiety is an exciting prospect. Not only could such an intervention lead to fewer anxiety symptoms in pregnant women with an established risk factor (RNT), it also has the potential to reduce the need for specialist, costly, high-intensity mental health support in the postnatal period (e.g. individual cognitive behaviour therapy).

### Objectives {7}

We will conduct a parallel two-arm randomised controlled trial to establish the efficacy of a multi-session, web-based CBM-I intervention tailored to women in the perinatal period (RELAX) in reducing anxiety in pregnancy and postpartum compared to usual care (UC) alone. We hypothesise that pregnant women with high levels of RNT who complete RELAX (plus UC) will report lower levels of anxiety during pregnancy and after birth relative to pregnant women who receive just UC. We will focus on the key cognitive mechanism of testing whether interpretation bias mediates treatment effects, and whether interpretation bias prevents anxiety.

### Trial design {8}

A two-arm, parallel-group, multi-site, superiority, Phase 2b randomised controlled trial in which randomisation will be stratified by recruitment site, parity, and pregnancy complications. Pregnant women (16–28 weeks gestation) with high levels of RNT (RTQ-10 score ≥ 28) and up to a moderate level of anxiety (GAD-7 score < 15) will be randomly allocated to one of two conditions. Specifically, they will either be assigned to either the RELAX intervention in which they will complete 12 web-based Cognitive Bias Modification for Interpretation (CBM-I) training sessions in a 4 week period alongside their usual maternity care or will continue with their usual maternity care.

## Methods: participants, interventions and outcomes

### Study setting {9}

The intervention is being delivered online via the REducing Levels of AnXiety (RELAX) platform. The RELAX platform [31] was built and is hosted by Avegen, a digital healthcare company who deploy digital health applications through cloud-hosted, product development platforms [32].

### Eligibility criteria {10}

Inclusion criteria are as follows: pregnant women (16–28 weeks gestation); high level of self-reported RNT (RTQ-10 (trait) ≥ 28; [33–35]; up to only a moderate level of anxiety (GAD-7 < 15); aged ≥ 18 years; living in the UK; able to understand oral and written English; normal or corrected-to-normal hearing and vision; access to the internet on a PC, laptop or tablet (other than mobile phone); provision of an email address and phone number (for contact with the team). Initial eligibility is based on participant self-reported responses at screening.

Exclusion criteria are as follows: reporting symptoms consistent with a current psychiatric diagnosis (assessed via the clinical interview schedule revised (CIS-R); [36] at screening; current or past diagnosis of a psychotic disorder (e.g. schizophrenia), eating disorder, substance use disorder (e.g. alcohol dependence) and/or personality disorder (e.g. borderline personality disorder); current or recent history of risk (e.g. suicidal thoughts on the PHQ-9, item 9 > 1); suicide attempt within the past 2 years and/or self-harm within the last year; history of stillbirth, neonatal death, or multiple (i.e. ≥ 3) miscarriages; current participation in another study evaluating a treatment for a mental health problem; not being registered with a GP in the UK.

We use the term “women” to refer to those who are pregnant. We acknowledge that not all people who are pregnant and give birth identify as women, and it is important that evidence-based care for maternity, perinatal and postnatal health is inclusive. The study is open to anyone who is currently pregnant however they choose to identify, and we welcome all those who are eligible.

### Who will take informed consent? {26a}

Participants provide informed consent at the start of the baseline assessment and their electronically signed informed consent form will be submitted via the online RELAX platform.

#### Eligibility assessment and study outline call

Pregnant women interested in taking part will be able to register on the RELAX platform, where they can also access the Participant Information Sheet. Individuals who register and provide consent for screening will complete a series of validated questionnaires along with additional questions assessing their eligibility against the inclusion/exclusion criteria. Individuals will be asked to provide their full name, age, sex at birth, email address, phone number, GP, midwife and maternity service details, and indicate where they heard about the study. They will also be asked their number of weeks gestation, along with questions regarding their pathway of care, current/past pregnancy complications and parity (i.e. whether they have had previous live births).

Individuals will be notified that they are not eligible at the point at which they provide an answer to a question that renders them ineligible, i.e. they will not be asked to complete any further items in the screening survey. Individuals who are eligible after completion of the screening questionnaire will be emailed by the team to arrange a telephone call (i.e. study outline call).

The study outline call will take approximately 20 min. The researcher will provide more information about the study (e.g. outline time commitments, explain randomisation), verify details provided in the screening questionnaire and answer any questions. The presence of current suicidal thoughts is assessed on the study call, and a risk assessment is conducted if needed and appropriate action in keeping with the risk protocol will involve a clinician if appropriate, or additional signposting to support services. A risk assessment is also conducted if the potential participant marked “1” indicating “Several days” to item 9 “Thoughts that you would be better off dead or hurting yourself in some way” on the Patient Health Questionnaire (PHQ-9) at screening [37]. In the event that a participant indicates during the call that they are unable to commit to the study and/or complete the RELAX sessions under the timeframe/conditions specified (e.g. they do not have time to complete three sessions per week, are unable to generate mental images, or do not have access to a quiet space), they will be offered the option to not take part (if still potentially eligible) and will be reimbursed with a £5 voucher for their time. If at the end of the call the participant is eligible and willing to continue, they will be provided with information about completing the baseline (T0) assessment and sent the link to do this.

#### Baseline assessment

Participants will complete the baseline (T0) assessment via the online RELAX platform, within 10 days of their screening questionnaire, after which time the link will expire. Any participant who has not completed the assessment by that time will no longer be able to do so.^1^ As part of the baseline assessment, participants will first provide informed consent and then proceed to complete the baseline measures:

Demographic variables: date of birth, ethnicity, religion, relationship status, social support, highest level of education, employment status, pre-existing health condition, number of children, estimated due date.

The *Repetitive Thinking Questionnaire (RTQ-10 (trait))* [33] is a 10-item measure of trait RNT. Participants rate the extent to which each item (e.g. “I have thoughts or images about all my shortcomings, failings, faults, mistakes”) is true for them when they are distressed or upset. The highest score possible is 50, indicating the greatest level of RNT. The measure demonstrated high internal consistency in a clinical sample of individuals diagnosed with major depressive disorder, social phobia, GAD or dysthymia (*α* = 0.92, mean inter-item correlation = 0.53 [33], Cronbach’s *α* = 0.90 [28]).

The *Generalised Anxiety Disorder Questionnaire (GAD-7)* [38] is a 7-item measure of anxiety symptoms over the past 2 weeks (e.g. “Feelingnervous, anxious or on edge?”). Items are scored 0–3 where 0 as “not at all,” 1 = “several days,” 2 = “more than half the days” and 3 = “nearly every day.” The GAD-7 has good test–retest reliability (intraclass correlation = 0.83) [38], Cronbach’s *α* = 0.87 [28]).

The *Patient Health Questionnaire (PHQ-9)* [37] measures depressive symptoms over the past 2 weeks. Item ratings are summed to produce a total score from 0 to 27. Participants who score above 1 on item 9: “Thoughts that you would be better off dead or hurting yourself in some way” will not be eligible for inclusion in the trial. The PHQ-9 is a reliable and valid measure of depression severity (*α* = 0.86 in an Obstetrics-Gynaecology population [37], Cronbach’s *α* = 0.84 [28]).

The *Penn State Worry Questionnaire (PSWQ)* [39] measures worry (e.g. “My worries overwhelm me”) and participants rate each statement on a scale of 1 (“not at all typical of me”) to 5 (“very typical of me”). Test–retest reliability is high [39], Cronbach’s *α* = 0.83 [17].

The *Work and Social Adjustment Scale (WSAS)* [40] is a five-item measure of impaired functioning [40]. Item 1 assesses impact on ability to work, item 2 assesses impact on home management, item 3 assesses impact on social leisure activities, item 4 assesses impact on private leisure activities and item 5 assesses impact on close relationships. Scores range from 0 to 40, with high scores indicating more impaired work and social functioning. We modified the measure to make it possible for participants to mark N/A to item 1 which relates to work, and plan to prorate this item with an average score when analysing the data in keeping with clinical practice. Test–retest reliability correlation = 0.73, internal scale consistency ranged from *α* = 0.70–0.94 [40].

The *Perinatal Anxiety Screening Scale (PASS)* [41] measures anxiety in antenatal and postpartum women and contains 31 items. Participants rate how often they experience each item (e.g. “Fear that harm will come to the baby”) in the past month. Item ratings are summed to produce a total score between 0 and 93, with higher scores indicating greater levels of perinatal anxiety. Test–retest reliability for the PASS is good (correlation for global scores 0.74 [41], Cronbach’s *α* = 0.94 [28]).

The *Edinburgh Postnatal Depression Scale (EPDS)* [42] is a 10-item measure used to assess depression symptoms in pregnant participants. Higher score indicates more severe perinatal depression. The EPDS high test–retest reliability for total scores (ICC = 0.92) [43]. Cronbach’s *α* = 0.84 [28]).

The *Recognition Test* [27, 44] will be completed at baseline and T1 to measure interpretation bias. It has been adapted from previous research [25, 27, 28, 44] for the purpose of this trial, and contains 12 scenarios (half are pregnancy-related, and the remaining scenarios are non-pregnancy related). The trial team and Research Midwife checked all pregnancy scenarios to ensure they were up-to-date, relevant and factually correct.

In the first part of this task participants are presented with a title and ambiguous scenarios. The final word in each scenario is presented as a word fragment with missing letters. Participants are instructed to enter the first missing letter of the word fragment. In the second part of the task, participants are presented with the title of the scenario and a series of four statements. They are asked to rate the degree to which each statement is similar in meaning to the original scenario on a 4-point scale (i.e. very different, fairly different, fairly similar, or very similar in meaning). Two of the statements represent potential interpretations of the ambiguity. One is a positive target relating to a positive interpretation of the scenario, the other a negative target related to a negative interpretation of the scenario. The remaining two statements are unrelated to the scenario but are either positive or negative in valence. Higher similarity ratings for positive targets indicate a more positive interpretation of that scenario. An example of a pregnancy scenario is as follows:

##### Midwife diet advice

You are pregnant and meeting with your midwife. They ask you how you have been managing your diet. You mention to them that you have not been eating very well as sickness has put you off certain foods or large meals. From the look on their face, you can tell what they are going to say about your diet.

Has sickness put you off large meals? (Yes/No).

Positive target: Your midwife is understanding and suggests that the way you are managing your diet is fine.

Negative target: Your midwife is unsympathetic and stresses how important maintaining a healthy diet is for the baby.

Positive foil: Your midwife provides you with some useful advice for dealing with morning sickness.

Negative foil: Your midwife repeats something you have already mentioned and you get the feeling that they are not listening to what you have to say.

Mean scores for both positive and negative targets are calculated and an interpretation bias score is generated by subtracting mean positive targets from mean negative targets. There are two sets of ambiguous scenarios which are presented in counterbalanced order across T0 and T1 assessments across participants.

*Psychological contact and treatment form* (*past diagnosis of a mental health condition, current psychological treatment and mental health medication receipt, previous contact with a health professional in relation to your mental health).*

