#### Mechanistic outcome

The primary mechanistic outcome is the mean difference in interpretation bias (measured using the Recognition Test) at 4-week post-randomisation between arms, adjusting for baseline interpretation bias. The mediating effect of the intervention on GAD-7 at T2 via interpretation bias at T1 will also be evaluated.

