#### Mechanistic analysis sample size

Estimates of the mediation parameters from Hirsch, Krahe et al. [27] as follows: standardised estimate of the a path (effect of intervention on mediator) = 0.5, b path (effect of mediator on outcome) = 0.2, and c’ path (direct effect of intervention on outcome) = 0.15, providing parameters for Monte Carlo simulations with 10 K repetitions to calculate power in Mplus [47], a sample size of 268 would give > 99% power to detect the mechanistic action of the intervention on interpretation bias (a path), and 83% power to detect the indirect or mediated (a x b) effect of the intervention on GAD-7 via interpretation bias.

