### Implementation {16c}

The bespoke RELAX randomisation algorithm has been built into the platform by Avegen’s data team and programmers. Stratified randomisation will be carried out via the RELAX platform by Avegen in a 1:1 ratio using randomly permuted blocks with varying block sizes. Stratification is by recruitment site (GSTT vs KCH vs ESTH vs MCHT vs KCL), parity (0 vs not 0), and pregnancy complications (no pregnancy complications vs pregnancy complications). The information needed to classify participants based on the stratification variables will be gathered via the screening questionnaire (and verified on the study outline call). This information will be entered by the researchers into the researcher’s interface, providing the information required for randomisation.

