### Methods for additional analyses (e.G. Subgroup analyses) {20b}

#### Analysis of the mechanistic outcome/mediation analysis

To estimate the extent to which the intention to treat RELAX vs UC intervention effect on anxiety (GAD-7) at 8 weeks (primary) or 36 weeks (secondary) is mediated by interpretation bias (measured using the Recognition Test) at 4 weeks, we will use linear structural equation models estimated using full information maximum likelihood estimation to fit mediation models. We will fit two separate structural equation models for the 8-week and 36-week GAD-7 outcome measures, each fitting two equations: one with the 4-week interpretation bias (RT) mediator as the dependent variable and the other with the GAD-7 outcome as the dependent variable with the RT mediator as an independent variable. Both mediator and outcome models will have arm as a binary independent variable, include the three randomisation stratification factors and the weeks of gestation at baseline variable as independent variables, and will include baseline GAD-7 and interpretation bias (RT) measures as independent variables.

The indirect (or mediated) effect will be calculated in each case by multiplying the estimate of the effect of the intervention on the interpretation bias mediator by the estimate of the effect of interpretation bias on the GAD-7 outcome. For this indirect effect, we will present the percentile bootstrap confidence interval from bootstrapping with 1000 repetitions [51]. We will also present this proportion of the total effect that mediated for each model, calculated as the indirect effect estimate divided by the total effect estimate, multiplied by 100.

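### Scenario-set order of the Recognition Test is missing from the listed covariates; if the two sets differ in mean score, the mediator carries avoidable noise

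*Protocol article*

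**What the plan says.** The Protocol article describes the Recognition Test under Baseline assessment. After the worked example it states: "There are two sets of ambiguous scenarios which are presented in counterbalanced order across T0 and T1 assessments across participants". Each woman therefore meets one set at T0 and the other at T1, and the order differs between women by design.

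The Mechanistic outcome section defines the primary mechanistic outcome as the mean difference in interpretation bias "at 4-week post-randomisation between arms, adjusting for baseline interpretation bias". No other adjustment is named there.

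The section on analysis of the mechanistic outcome and mediation lists the covariates: "Both mediator and outcome models will have arm as a binary independent variable, include the three randomisation stratification factors and the weeks of gestation". It adds that the models "will include baseline GAD-7 and interpretation bias (RT) measures as independent variables". Neither set nor set order appears.

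Order does not enter through the stratification factors either: "Stratification is by recruitment site (GSTT vs KCH vs ESTH vs MCHT vs KCL), parity (0 vs not 0), and pregnancy complications".

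**The concern.** Counterbalancing stops a difference between the sets from being mistaken for change over time. It does not remove the variance that such a difference creates. If one set draws more negative ratings than the other, women who get it at T0 score high at T0 and low at T1, relative to women with the reverse order. The set difference thus inflates the variance at both times and lowers the correlation between them. Baseline adjustment cannot absorb it, and itself works less well.

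Two things are at stake: the precision of the 4-week arm comparison, and the b path. For the b path the set component acts as measurement error in the mediator and pulls the estimate, and with it the indirect effect, towards zero.

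Equality of the sets cannot be taken for granted. The test was adapted for this trial, and the only check described concerns the content of the pregnancy scenarios (currency, relevance, accuracy), not equal mean scores between sets.

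**Working it through.** **Inputs from the document.** N = 268; "standardised estimate of the a path (effect of intervention on mediator) = 0.5"; b path 0.2; direct effect 0.15; stated power 83% for the indirect effect and above 99% for the a path (Mechanistic analysis sample size). **Assumed, not in the document:** the set difference d, in SD of the Recognition Test score, and the T0-T1 correlation ρ, taken as 0.5 with 0.6 as a check.

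**Step 1: reproduce the plan's figure.** A Monte Carlo run used 20,000 repetitions, N = 268, fully standardised paths, no attrition, two-sided 5% and no set effect. The delta-method (Sobel) test gave 83.1%, the joint-significance test 84.3%, and the a path about 100%. The stated 83% and >99% reproduce.

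**Step 2: residual variance of the 4-week score.** Code order o as ±0.5. T1 gains +d·o and T0 gains −d·o, and d·o has variance d²/4. So:

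- V = Var(T0) = Var(T1) = 1 + d²/4
- C = Cov(T0, T1) = ρ − d²/4
- residual variance of T1 given T0 = V − C²/V, against 1 − ρ² when order is in the model

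For ρ = 0.5 the reference is 0.75:

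| d | V | C | Residual | Ratio to 0.75 | Interval width (square root) |
|---|---|---|---|---|---|
| 0.2 | 1.0100 | 0.4900 | 0.772 | 1.03 | +1.5% |
| 0.3 | 1.0225 | 0.4775 | 0.800 | 1.07 | +3% |
| 0.5 | 1.0625 | 0.4375 | 0.882 | 1.18 | +8.5% |

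For ρ = 0.6 (reference 0.64) the variance increases are 4%, 9% and 24%. For d = 0 the increase is zero.

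**Step 3: attenuation of b (baseline score not in the model).** Given arm, the mediator variance is 1 − 0.5² = 0.75. The set component adds d²/4, so b shrinks by the factor 0.75/(0.75 + d²/4):

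- d = 0.2: 0.75/0.76 = 0.987, a loss of 1.3%
- d = 0.5: 0.75/0.8125 = 0.923, a loss of 7.7%
- d = 0.8: 0.75/0.91 = 0.824, a loss of 17.6%

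**Step 4: power for the indirect effect.** Same set-up as Step 1, 8,000 repetitions per cell, Sobel test:

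| d | Order omitted | Order included |
|---|---|---|
| 0.2 | 82.5% | 83.0% |
| 0.3 | 82.4% | 83.3% |
| 0.5 | 79.5% | 82.9% |
| 0.8 | 75.2% | 83.2% |

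The simulation standard error is about √(0.83 × 0.17/8000) = 0.4 points, so differences up to 0.3 SD are close to simulation noise. The a path stays at about 100% throughout.

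**Step 5: two variants.**

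- *Baseline Recognition Test in both equations, ρ = 0.5.* This is nearer to the planned model. Power is lower overall because baseline takes up part of the mediator's variance. The comparison is 68.0% without order against 71.4% with it at 0.5 SD, and 65.7% against 72.1% at 0.8 SD. That is a loss of about 3 and 6 points.
- *Arm coded 0/1 with a = 0.5 SD.* This fits the stated 83% less well (80.9%). The losses are slightly larger: 78.8% against 80.2% at 0.3 SD (1.4 points) and 75.9% against 80.8% at 0.5 SD (4.9 points). The a path keeps 96% power even at 1 SD.

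**The case against.** The strongest reply is that nothing here is an error. Counterbalancing is itself the safeguard. Baseline is completed before randomisation, so order is in place before allocation. If allocation ignores order, as the stratification list suggests, the arm difference in interpretation bias is unbiased. The document does not say that the sets differ, the loss is small over most of the range shown, and an article need not list every covariate that an analysis plan contains.

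Most of this stands, and it rules out several stronger readings that a reader might infer:

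- *That omitting order biases the mechanistic arm effect.* It does not if order is independent of arm. The document does not say how order is assigned relative to arm, but nothing in it suggests dependence.
- *That order is certain to add noise.* It does so only if the sets differ in mean score, and no such figure is given.
- *That mediation power is already short, so any loss is serious.* The stated 83% reproduces for all 268 women. What attrition does to it is a separate question and is not part of this point.
- *That there are two sets of 12 scenarios.* The text gives 12 scenarios and two sets, without saying whether 12 is per set or in total.
- *That the final analysis will omit order.* The approved analysis plan is not shown and may include it.

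What does not fall is the narrow point. The article does spell out a covariate list for these models, and a factor that the design itself creates is absent from it. Counterbalancing protects against bias, not against lost precision.

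**Conclusion.** The point holds as a conditional efficiency improvement, not as an error or contradiction. If the two sets differ in mean bias score, leaving order out raises the residual variance of the 4-week score by about 3%, 7% and 18% at 0.2, 0.3 and 0.5 SD (intervals wider by about 1.5%, 3% and 8.5%). It weakens the b path mildly. In the calculation that reproduces the plan's 83%, it costs under 1 point of indirect-effect power up to 0.3 SD and about 3 to 4 points at 0.5 SD. The conclusion on the a path would hardly change.

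The sizes rest on an assumed set difference, and the variance figures also on an assumed T0-T1 correlation of 0.5; the document supplies neither. With matched sets the loss is nil.

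**What to change.** Pre-specify set order (A-B versus B-A) as a binary covariate in the 4-week interpretation bias model and in both the mediator and outcome equations of the 8-week and 36-week mediation models. State that order is assigned independently of arm. If the analysis plan already has the term, bring the published covariate list into line with it.

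The cost is one degree of freedom per equation. No new data collection should be needed: the platform has to know which set a woman saw at T0 in order to show the other at T1, although the document does not say that this is stored. Fixing the term before the data are seen keeps it from becoming a discretionary choice.
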